### Study procedure

The duration of this study will be 3 years, with 1 year of enrollment and a minimum follow-up period of 2 years. The specific measurements and time points for data collection of this study are outlined in Fig. 2, which must be followed as accurately as possible. Treatment will be started within 7 days of the randomization and last for 6 months. Eligible patients will be followed up every 3 months until death or the end of this study. The researcher should obtain written informed consent before conducting study-specific procedures for patients enrolled in the trial.

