#### Secondary outcomes

One, two-year relapse rate (RR): RR is defined as the fraction of followed patients who have disease recurrence. All disease recurrences and deaths from colon cancer are events. Second primary same cancers and other primary cancers will be ignored.

Overall survival (OS): OS is measured from the date of enrollment to the date of death, irrespective of cause.

Quality of life (QoL):

1. Changes in total score on the EORTCQLQ-C30 Scale: The changes of EORTCQLQ-C30 score will be compared in the two groups prior to and following XLJDOD compound granule administration. Considering that some items of EORTC QLQ-CR29 scale are targeted at colostomy patients with rectal cancer, we select the EORTCQLQ-C30 Scale. It is a universal scale for all patients with malignant tumors with a total score of 126, ranging from 30 (least severe) to 126 (most severe). Measurement will be performed at baseline and month 6, 12 ,18 ,24.

2. Changes in total score on the MD Anderson Symptom Inventory for Traditional Chinese Medicine (MDASI-TCM): Compared with the baseline period, the changes in MDASI-TCM score at month 6, 12 ,18 ,24 will be measured. The scale is divided into two parts. The first part mainly assesses the severity of 20 common clinical symptoms and TCM-related symptoms of patients with cancer in the past 24 hours. The second part is the evaluation scale of the interference of the above symptoms with daily functioning [33]. It has a total of 26 items, each with a score of 0–10, leading to a total score of 0–260.

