### Sample size calculation

The primary Outcome of this study is the rate of 2-year DFS in stage IIIB or IIIC colon cancer. Based on the literature and previous study, it is assumed that the 2-year DFS rate of control group is 0.70 (70%) and of the intervention group is 0.80 (80%). Taking a two-sided significance level of 5% and power of 80% (α = 0.05, β = 0.10), the intervention group and the control group are allocated at a ratio of 1:1. Considering a dropout rate of 20%, the sample size is not less than 364 cases in each group. Therefore, a total sample size of 730 cases is set up in this study (*n* = 365 in each group).

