#### Content and method of statistical analysis

The statistical analysis plan will be developed by an independent statistician who does not participate in the study in consultation with the principal researchers. SAS 9.4 will be employed for statistical analysis. The content will cover actual number of subjects enrolled in both groups, shedding and exclusion of cases, demographics and other baseline characteristics, compliance, efficacy analysis, and safety analysis.

The description of qualitative data will use frequency table, percentage or proportion. Quantitative data will be expressed by mean, standard deviation, median (P25, P75) and minimum/maximum values.

The Log-rank test will be used as the primary analysis for comparison of 2-year DFS rate in two groups, and the Cox regression will be used to adjust for covariates (such as study centers) as sensitivity analysis. Pre-determined subgroup analysis factors include sex, age (< 65 yr versus ≥ 65 yr), tumor location (left colon versus right colon), tumor pathological stage (IIIB versus IIIC), T classification (T1, T2, or T3 versus T4), N classification (N1 versus N2), the presence or absence of venous invasion. The comparison of 1,2-year RR and median OS will be performed by Log-rank test. The QoL score at different time points will be analyzed using mixed effect model and adjusting for study centers. Safety outcomes will be evaluated by summarizing the number of abnormal subjects and comparing the rate between groups. All data statistics will be analyzed by using a two-sided test, and the test statistics and their corresponding *p*-values will be given, with a significance level setting at *p* < 0.05.

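### Median OS will not be reached on the protocol's own assumptions, and relapse rate is defined as a crude fraction that its log-rank test does not compare

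*Protocol article*

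**What the plan says.** Under Content and method of statistical analysis, the protocol article plans: "The comparison of 1,2-year RR and median OS will be performed by Log-rank test".

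The endpoints themselves are defined under Secondary outcomes:

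- Relapse rate: "RR is defined as the fraction of followed patients who have disease recurrence". Recurrences and deaths from colon cancer count as events, and second primaries are ignored. The word *followed* is not explained.
- OS: "OS is measured from the date of enrollment to the date of death, irrespective of cause". This is a time-to-event definition and does not mention a median.

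Three other statements bear on the point:

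- Under Primary outcome, death from any cause is one of the DFS events.
- Under Study procedure: "The duration of this study will be 3 years, with 1 year of enrollment and a minimum follow-up period of 2 years".
- Under Sample size calculation, 2-year DFS is taken as 70% on control and 80% on intervention, and dropout enters as follows: "Considering a dropout rate of 20%, the sample size is not less than 364 cases in each group".

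**The concern.** A median can be estimated only once the survival curve has fallen to 50%. If the trial's own assumptions keep OS well above that throughout follow-up, the quantity named for the OS comparison would be reported as not reached in both arms, and the plan names no other OS summary.

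For relapse, the definition and the test describe different things. A fraction of patients is a simple proportion. A log-rank test compares whole time-to-event curves and handles censored patients. The reported percentages and the p-value beside them would therefore answer different questions. The percentages would also depend on how patients lost before 12 or 24 months are counted, which the definition leaves open. What is at stake is the reported size of effect on two secondary outcomes.

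**Working it through.** **1. The plan's own figure.** Two proportions, unpooled variance, two-sided 5%, 80% power:

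- n = (1.960 + 0.842)² × (0.70 × 0.30 + 0.80 × 0.20) / 0.10² = 290.4, so 291 per arm.
- 291 / (1 − 0.20) = 363.75, so 364 per arm, as stated.

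The 70%, 80% and 20% used below are thus the figures the sample size really rests on. (The same sentence prints β = 0.10. At 90% power this formula gives 389, then 487 after dropout, so the stated size matches 80% power.)

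**2. A floor for OS.** Every death is a DFS event, so OS(t) ≥ DFS(t) at all times. One year of enrolment plus a 2-year minimum gives each patient 24 to 36 months.

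- At 24 months, OS is at least 70% and 80%.
- At 36 months with constant hazard, DFS is 0.70^1.5 = 58.6% and 0.80^1.5 = 71.6%. OS is at least that.
- Median DFS at constant hazard is 2 × ln 2 / (−ln 0.70) = 3.9 years and 2 × ln 2 / (−ln 0.80) = 6.2 years, both beyond the 3-year maximum.

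What it would take to reach a median within 36 months:

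- At constant hazard, 2-year OS would have to be 0.5^(2/3) = 63% or lower, which is below the DFS assumed for control.
- For control DFS merely to touch 50% at month 36, its hazard would have to rise from −ln(0.70)/24 = 0.0149 to ln(0.70/0.50)/12 = 0.0280 per month after month 24. For OS to follow, every DFS event would also have to be a death by then. The Introduction puts the highest recurrence risk in the first 2 years.
- In a population made up only of stage IIIC (60% DFS at 2 years in the Introduction), the constant-hazard DFS median is 2.7 years. That is DFS rather than OS, and one stratum rather than the trial.

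**3. Relapse as a crude fraction.** Assumptions: relapse and loss to follow-up each have constant hazard and are independent; the 20% is all loss to follow-up over 24 months; true 2-year relapse equals 1 − DFS, i.e. 30% and 20%. The last slightly overstates relapse, because DFS also counts second primaries and other deaths.

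With h = −ln(DFS)/24 and c = −ln(0.80)/24:

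- Relapse seen before loss = h/(h + c) × (1 − DFS × 0.80). Control: 0.615 × 0.44 = 27.1%. Intervention: 0.500 × 0.36 = 18.0%.
- Lost without relapse = c/(h + c) × (1 − DFS × 0.80). Control: 16.9%. Intervention: 18.0%.
- With those patients removed from the denominator: 0.2707/0.8307 = 32.6% and 0.180/0.820 = 22.0%.

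| Reading of *followed* | Control (true 30%) | Intervention (true 20%) | Difference (true 10 points) |
|---|---|---|---|
| All patients in denominator | 27.1% | 18.0% | 9.1 |
| Event-free dropouts removed | 32.6% | 22.0% | 10.6 |

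Sensitivity:

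- With dropout from 10% to 30%, the control figure runs from 28.6% to 25.5% on the first reading and from 31.2% to 34.2% on the second.
- If the whole 20% left at time zero, the first reading gives 24% and 16%, and the second gives the true 30% and 20%.

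Under non-informative loss, a Kaplan-Meier or cumulative-incidence estimate recovers 30% and 20% in this set-up.

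**The case against.** The strongest reply is that little is actually broken. OS is defined as time to death, a log-rank test needs no median, and the analysis section promises test statistics and p-values. A log-rank test on time to relapse also handles censoring properly. This stands. A reader might infer that the OS endpoint cannot be analysed at all; the documents do not support that. The defect lies in the summaries named, not in the tests.

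A reader might also infer that the relapse rate is bound to understate relapse. That does not follow either. The direction depends on the unexplained denominator, and removing event-free dropouts overstates relapse by a similar amount. The 20% is a sample-size allowance of unstated timing. The Withdrawal criteria include non-compliance and unblinding, after which recurrence might still be recorded.

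Several neighbouring points should not be pressed:

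- The 2-year minimum follow-up means staggered entry does not cut short the 1- or 2-year rates; only dropout does.
- Truncation of each test at 12 and 24 months can be left to the statistical analysis plan, and a particular test for cumulative-incidence curves is a preference.
- OS starting at enrolment while DFS starts at randomisation may be terminology only. Trial status speaks of enrolling patients into the two groups, and no gap between the dates is given.

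The Discussion concedes that follow-up for DFS and OS is short and plans to continue it if the treatment is effective. That shows awareness, but a conditional extension does not make the median available to the planned analysis.

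**Conclusion.** The point holds for two summaries. Median OS will not be reached in either arm on the protocol's own figures. The bounds of 70% and 80% at 24 months need only the planning assumptions; those of 58.6% and 71.6% at 36 months also need a constant DFS hazard. The crude relapse fraction does not match its log-rank test, and under the illustrative 20% loss it would miss the true 2-year rates by about 2 to 3 points in either direction. That size rests on independent loss at a constant rate and on relapse being set to 1 − DFS.

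The log-rank comparisons of OS and of time to relapse remain valid. The primary endpoint and the sample size are not affected. The change is worth making because it alters reported secondary results at almost no cost.

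**What to change.** - **OS:** keep the log-rank test. Report the hazard ratio with 95% CI and Kaplan-Meier OS at 24 months in each arm. Give the median only if it is reached.
- **Relapse rate:** redefine it as the cumulative incidence of relapse at 12 and 24 months in all randomised patients, with patients censored when lost and deaths not from colon cancer treated as a competing event. Give the between-group difference with 95% CI at each time.

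No new visits, patients or data are needed. Event dates are required for DFS and OS already, and the present relapse definition already requires deaths from colon cancer to be told apart from other deaths. The cost is a change of wording and a little more analysis work on secondary endpoints.

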### Randomization and allocation concealment

In this trial, an online centralized randomization system called Interactive Web Response System (IWRS) will perform the block randomization with a 1:1 ratio, permutation block with variable sizes of four, six, eight, or twelve, stratified by the study center. After informed consent, the investigators will log into IWRS to acquire a unique identification code and random number of each participant for participant identification and treatment assignment. IWRS will ensure the allocation concealment. It will only offer a random number to the investigator, and none of the investigators, participants, and outcome evaluators will know from random numbers whether they represent the intervention group or the control group. In case of SAEs that may be associated with experimental drugs, including death, allergic reactions, intolerable severe gastrointestinal reactions, liver and kidney insufficiency, etc., the allocated intervention of participant could be revealed by investigator in the IWRS.

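### The quality-of-life mixed model names only study centre as an adjustment; fitted as worded, it is less precise than a model that uses the baseline scores the trial already collects

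*Protocol article*

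**What the plan says.** In the protocol article, under Content and method of statistical analysis, the whole specification for quality of life is: "The QoL score at different time points will be analyzed using mixed effect model and adjusting for study centers". Centre is the only adjustment named. In the same paragraph the Cox sentence gives centre merely as an example of its covariates, so its list is left open; the quality-of-life sentence has no such opening.

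Under Secondary outcomes, the first quality-of-life outcome is "Changes in total score on the EORTCQLQ-C30 Scale", with this schedule: "Measurement will be performed at baseline and month 6, 12 ,18 ,24". The second is worded similarly: "Compared with the baseline period, the changes in MDASI-TCM score at month 6, 12 ,18 ,24 will be measured". Both outcomes are therefore changes, and both need a baseline score.

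Allocation is "stratified by the study center" and by nothing else, so baseline quality of life is not balanced by design. The analysis plan is still to come: "The statistical analysis plan will be developed by an independent statistician who does not participate in the study".

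**The concern.** The outcome definitions speak of changes, while the analysis sentence speaks of the score at different time points. The text does not settle whether the modelled response is the score or the change, whether baseline is one of the time points, or whether the baseline score is a covariate. These choices give different estimates whenever the arms differ at baseline by chance, and they differ in precision.

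Quality of life is a named secondary outcome and part of the trial's stated aim. A sentence that names centre and stops there is what the author of the analysis plan would take over. Followed literally, it leaves unused a covariate that has already been collected.

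**Working it through.** **Inputs.** From the protocol article: baseline and four follow-up visits; 1:1 allocation with 365 per arm; 20% dropout, which leaves 365 × 0.80 = 292 per arm. Not in the document, hence assumed: the correlation ρ between baseline and follow-up score, taken as 0.4 to 0.6, and equal standard deviation (SD) at both times, so that the score variance is 1.

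**Plan's own figure.** The article gives no precision or power figure for quality of life, so there is none to reproduce. The 365 per arm comes from the disease-free survival calculation and serves here only as n.

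**Step 1: variance at one visit.** The between-arm contrast has variance (2/n) × v, where

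- raw follow-up score: v = 1
- change score: v = 1 + 1 − 2ρ = 2(1 − ρ)
- follow-up score adjusted for baseline: v = 1 − ρ²

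The gain from adjustment is 1 − (1 − ρ²) = ρ² against the raw score, and 2(1 − ρ) − (1 − ρ²) = (1 − ρ)² against the change score. Both are positive for every ρ strictly between 0 and 1.

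| ρ (assumed) | raw | change | adjusted | cut against raw | cut against change |
|---|---|---|---|---|---|
| 0.4 | 1 | 1.20 | 0.84 | 16% | 30% |
| 0.5 | 1 | 1.00 | 0.75 | 25% | 25% |
| 0.6 | 1 | 0.80 | 0.64 | 36% | 20% |

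**Step 2: in terms of power.** Take an effect that gives 80% power on the raw score. At ρ = 0.4, 0.5 and 0.6 the change score gives 72.5%, 80.0% and 87.9%; the adjusted analysis gives 86.4%, 89.9% and 93.8%.

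**Step 3: baseline as one of the repeated responses.** Suppose the mixed model includes the baseline visit and lets the arms have different baseline means. With complete data, the treatment-by-time contrast is then the difference in mean change, with v = 2(1 − ρ), and the arm difference at a later visit is the raw contrast, with v = 1. Neither reaches 1 − ρ². Constraining the baseline means to be equal, which randomisation justifies, brings the precision essentially to that of baseline adjustment.

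**Step 4: chance imbalance.** With 365 per arm, the baseline difference at its 95% limit is 1.96 × √(2/365) = 0.145 SD (0.162 SD with 292). Given such a difference, the raw comparison shifts by ρ × 0.145 = 0.058, 0.073 and 0.087 SD at ρ = 0.4, 0.5 and 0.6. The change comparison shifts by (1 − ρ) × 0.145 = 0.087, 0.073 and 0.058 SD in the opposite direction. For scale, the standard error of the raw contrast is √(2/365) = 0.074 SD.

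**The case against.** The strongest reply is that this is a condensed article with an analysis plan still to be written, and that the covariates of a secondary-outcome model usually sit there. The sentence is silent on baseline and does not rule it out. Both outcomes are defined as changes, so baseline is already used in some form, and a model of scores over time may well include the baseline visit. The correlation is assumed, and the variance figures are for one visit while four are modelled together.

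Much of this stands. A reader might infer that the protocol excludes the baseline score; it does not say so. A reader might also infer that the comparison will be biased; randomisation keeps it unbiased on average, and the shifts in step 4 are conditional on an unlucky imbalance. The size of the loss cannot be fixed from the document.

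Three parts do not stand. The article does more than leave the adjustment open: it names one and stops, unlike its own Cox sentence. Using baseline through a change score, or as an unconstrained response, does not recover the precision (steps 1 and 3). Nor does working at one visit flatter the result. If all visits correlate at 0.5, the mean of the four follow-up visits has v = (1 + 3 × 0.5)/4 = 0.625 for the raw score, 0.625 + 1 − 2 × 0.5 = 0.625 for the change and 0.625 − 0.5² = 0.375 after adjustment, a cut of 40%.

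The stated QLQ-C30 range, "ranging from 30 (least severe) to 126 (most severe", might lead a reader to infer that some items run in opposite directions within the total. The document lists neither the items nor their directions, and reversing an item leaves the range unchanged, so this is not supported and forms no part of the point.

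**Conclusion.** The point holds as a worthwhile improvement, not as an error that threatens the trial. Fitted as worded, in any of the three forms considered, the quality-of-life comparison is less precise than a baseline-adjusted one for any correlation strictly between 0 and 1. With equal variances and an assumed correlation of 0.4 to 0.6, the recoverable variance at one visit is 16% to 36% against the raw score and 30% to 20% against the change score. If the eventual analysis plan includes baseline as a covariate or as a constrained response, nothing is lost. Only a secondary outcome is affected; the disease-free survival analysis is not.

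**What to change.** State the model for each instrument as: score at months 6, 12, 18 and 24 on treatment, visit, treatment × visit, baseline score, baseline × visit and centre. Equivalently for this purpose, keep baseline among the repeated responses with the arm means constrained equal at baseline. Present the treatment contrast at each visit from that model as the estimate for the change outcomes: once baseline is a covariate, modelling the score or the change gives the same treatment contrast, which brings the analysis into line with the outcome definitions.

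The cost is a sentence in the analysis plan, settled before unblinding. The baseline scores are already scheduled, so no new data, visits or patients are needed.

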## Discussion

Colorectal cancer is the second most common malignant tumor in China, with a continuous increasing trend for incidence and mortality rates [34]. 3–6 months of adjuvant 5-FU-based chemotherapy is standard for patients with stage III colon cancer after completion of surgery, and then followed by surveillance. However, there remains room for improvement in DFS of stage IIIB or IIIC colon cancer patients with high risk of recurrence. Thus, in addition to adequate surveillance, novel therapeutic strategies after adjuvant chemotherapy are required to achieve more favorable clinical efficacy.

Although many studies [35–39] have demonstrated that the low-dose use of NSAIDs, in particular Aspirin, is associated with the decreased risk of postoperative recurrence and death of colon cancer, this was not confirmed in a large randomized controlled trial [40]. Additionally, increasing studies have examined the association between vitamin D [41–43], metformin [44–47] and the recurrence and mortality of colon cancer, but generated conflicting conclusions. In the meantime, the side effects hamper the acceptance of these strategies as adjuvant agents in colon cancer.

TCM has the advantages of reliable efficacy and low treatment cost. It has been widely used in the treatment of different malignant tumors. Surveys indicate that approximately 80 percent of patients in China had used TCM, particularly CHM, during cancer treatment [48, 49]. Mounting evidence, meanwhile, suggests that Chinese medicine prescriptions have significant effect of colon cancer progression control [16, 20, 50–53]. XLJDOD is an empirical prescription used as an adjuvant treatment of colorectal cancer for more than 10 years in China. Basic biological research confirms that XLJDOD effectively inhibits tumor cell proliferation and migration, modulates tumor microenvironment, regulates the function of immune cells [54–56].

The goal of this large sample size, multicentre randomized controlled trial is to evaluate the efficacy and safety of XLJDOD as an adjuvant treatment for prevention of stage IIIB or IIIC colon cancer recurrence and to evaluate whether it can prolong survival and promote QoL. Furthermore, if the trial proves that taking XLJDOD after adjuvant chemotherapy is more potent and efficient than Placebo in reducing the risk of tumor recurrence, we will explore the mechanism of XLJDOD in the treatment of colon cancer by the plasma collected before and after the intervention.

However, this study has certain limitations. First of all, the duration of CHM therapy is relatively limited. This is due to the consideration that CHM therapy use for at least 6 months can be regarded as an effective high exposure [57], and longer duration of CHM use can lead to decreased compliance and increased rate of lost-to-follow-up. Secondly, the duration of follow-up for DFS and OS is relatively insufficient. In this study, we will primarily assess the efficacy of XLJDOD in the first 2 years after adjuvant therapy. If effective, the follow-up will be continued beyond the end of the study.

To our best knowledge, this trial represents the first attempt to evaluate CHM as an adjuvant agent after completion of surgery and standard adjuvant chemotherapy in stage IIIB or IIIC colon cancer. If shown to be beneficial, the results will provide a treatment strategy of TCM, which can be extensively and successfully used in clinical practice.

